## 6. DOSING REGIMENS AND TREATMENT GROUPS

Across the 4 University of Oxford-sponsored studies, participants were randomized to receive a single dose or two doses of either AZD1222, ranging from  $2.2$  to  $5.0 \times 10^{10}$  vp, or control (as described in [Table 4](#)). AZD1222 CTM was sourced from: 1) CBF at the University of Oxford; 2) Advent, Italy, and 3) Cobra Biologics. For control, the MenACWY vaccine was administered in Studies COV001, COV002, and the first dose of COV003, and 0.9% normal saline (0.9% NaCl) was administered in Study COV005 and the second dose of Study COV003 for participants who received two doses.

[Table 4](#) presents the actual AZD1222 dose levels participants received across the 4 studies by the CTM source and SD or LD designation. For the pooled analyses, a designation of SD or LD was given to each of the AZD1222 dose levels. Generally,  $5 \times 10^{10}$  vp or equivalent is designated as a SD, and  $2.2 \times 10^{10}$  vp or  $2.5 \times 10^{10}$  vp are designated as a LD. Due to a potency miscalculation, participants in Study COV002 groups 1, 2, 4 and 5a who were to receive  $5 \times 10^{10}$  vp (Abs260) Advent as the first dose per protocol, received a lower dose of approximately  $2 \times 10^{10}$  vp (qPCR). Study COV005 groups 1 and 2 also had the LD vaccine.

Table 4 Actual AZD1222 Dose Levels Received by CTM and HD or LD Designation

| AZD1222 Dose Level                             | SD/LD |
|------------------------------------------------|-------|
| $2.2 \times 10^{10}$ vp (qPCR) Advent material | LD    |
| $2.5 \times 10^{10}$ vp (qPCR) Advent material | LD    |

| AZD1222 Dose Level                               | SD/LD |
|--------------------------------------------------|-------|
| 3.5 - 6.5 × 10  vp Cobra material   | SD    |
| 5 × 10  vp (Abs260) Advent material | LD    |
| 5 × 10  vp (qPCR) Advent material   | SD    |
| 5 × 10  vp Advent material          | SD    |
| 5 × 10  vp CBF material             | SD    |

CTM = Clinical Trial Material; LD = low dose; SD = standard dose; vp = viral particles.

One source of heterogeneity relates to logistical constraints in the context of the rapid conditions in which this clinical program and scale up manufacturing were initiated in parallel, which led to delays in clinical study material availability for second dose vaccinations in studies to be included in the pooled analyses. This resulted in the fact that, for some participants, the interval between the first and second doses (ie, dose schedule) exceeded 1 month. Dose schedule of two doses will be summarized and homogeneity among different dose schedules will be investigated when needed.

## 7. OVERVIEW OF ANALYSIS CONVENTIONS

### 7.1 Data Presentation

The planned 5% alpha will be split across the interim and primary analyses as described in Section 4.1. All efficacy analyses will use a 2-sided alpha test unless otherwise stated. P values will be rounded to 4 decimal places. If a p value is less than 0.0001, it will be reported as “< 0.0001”. If a p value is greater than 0.9999, it will be reported as “> 0.9999”.

All continuous variables will be summarized using descriptive statistics, reporting N, mean, standard deviation, median, minimum, and maximum. As appropriate, minima and maxima will be reported with the same precision as the raw values; medians and means will have one additional decimal place; standard deviation will have 2 additional decimal places. Data will be displayed by treatment group in all listings, as needed. Participants will be uniquely identified in the listings by the combination of study number, study site number, and subject number.

For discrete, or categorical data, percentages will be suppressed when the count is zero. A row denoted as “Missing” will be included in the count tabulations where necessary to account for dropouts or missing values.

All regulatory analyses will be performed using SAS®, Version 9.4 or higher (SAS Institute Inc., Cary, NC).

## 7.2 Definitions of Subgroups

To explore the implications for efficacy, safety, and immunogenicity among different populations, the following subgroups will be used:

- Age at randomization;
  - 18-64, 65 years and above
  - 18-55, 56-69, 70 years and above (for efficacy analysis of the primary manuscript only)
- Country (UK, Brazil vs South Africa)
- Comorbidity at baseline (at least one comorbidity vs no comorbidity), where comorbidity is BMI  $\geq 30$  kg/m^2 at baseline, Cardiovascular Disorder, Respiratory disease or Diabetes.
- Baseline serostatus (seronegative vs seropositive)

The analyses by each subgroup will be performed for all endpoints (efficacy, safety, and immunogenicity) unless specified otherwise.

Additional subgroups which may be explored include but are not limited to:

- Gender (male, female)
- Race (Asian, Black, White, Mixed, Other, Unknown): only categories with at least 100 individuals exposed will be presented
- Use of prophylactic paracetamol (for analysis of reactogenicity)
- Dose level (LD/SD vs SD/SD)
- Dose schedule (< 6 weeks, 6-8 weeks, 9-11 weeks,  $\geq 12$  weeks)
- Control type (MenACWY, Saline) (for safety only)

## 7.3 Definition of Baseline

In general, the last non-missing measurement collected prior to the first dose is considered as baseline. If the change from the second dose of study intervention needs be calculated, the last non-missing assessment collected prior to the second dose of study intervention will be considered as baseline.

## 7.4 Handling of Missing Data

As a general rule, missing data values will not be imputed unless otherwise specified below.

In the summary of AEs by timing relative to each vaccination, if the AE onset date is completely missing, then the AE will be included in summary. If the AE onset date is partially missing, partial AE dates will be handled using the following imputation rules:

- Partial AE start dates where only the year is known:

- If the year is same as the year of dosing:
  - Assume (first dose date + 1 day) if when AE occurred relative to dosing is not available
  - Assume dose date if otherwise
- If the year is not same as the year of dosing, assume January 1 for start date
- Partial AE stop dates where only the year is known: assume December 31 for stop date. If imputed date is greater than the cut-off date of data, use cut-off date instead.
- Partial AE start dates where only the month and year are known:
  - If the year and the month are the same as the year and the month of dosing:
    - Assume (dose date + 1 day) if when AE occurred relative to dosing is not available
    - Assume dose date if otherwise
  - If the year and the month is not same as the year and the month of dosing: assume the first of the month for start date.
- Partial AE stop dates where only the month and year are known: assume the end of the month for stop date

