## 7.5 Reference Start Date and Study Day

Study Day will be calculated from the reference start date and will be used to show start/stop day of assessments and events. Reference start date is defined as the day of the first dose of study drug intervention ie, Day 0.

Study Day will be computed as follows:

- Study Day = (Date of event – Date of first dose of study drug)

In addition, day relative to vaccination will be derived for each vaccination dose. For example, day relative to the first dose will be equal to the Study Day. Day relative to the second dose will start with a value of 0 on the day of the second dose.

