#### **10.1.5 Serious Adverse Events (SAEs)**

SAEs are those events recorded as “Serious” on the AE page of the eCRF. SAEs following the first vaccination to 364 days after the last vaccination will be summarized. Summaries will be produced of:

- Number of SAEs by treatment group, Medical Dictionary for Regulatory Activities (MedDRA) system organ class and preferred term
- Number of participants with SAEs by treatment group, system organ class and preferred term
- Number of participants with SAEs, assessed by investigator as possibly related to investigational product, by treatment group, system organ class and preferred term
- Number of participants with SAEs  $\geq x\%$  in either treatment group, by treatment and preferred term where x may be 1, 3 or 5

In the summary of number of participants, should a subject experience multiple events within a SOC or PT, the subject will be counted only once for that SOC or PT.

A listing of all SAEs including those prior to the first vaccination will be provided at the time of the primary analysis.

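### The partial-date rule in SAP 7.4 has no branch for adverse events known to start before the dose, and no check of the imputed start against the stop date

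*SAP*

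**What the plan says.** SAP section 7.4 opens its rules for adverse event dates in the context of summaries by timing relative to each vaccination, and then states: "If the AE onset date is partially missing, partial AE dates will be handled using the following imputation rules".

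For a start date in the same year as dosing (only the year known) or the same month as dosing (month and year known), there are two branches:

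- Timing relative to dosing unknown. Year only: "Assume (first dose date + 1 day) if when AE occurred relative to dosing is not available". Month and year: "Assume (dose date + 1 day) if when AE occurred relative to dosing is not available".
- Every other case, for both kinds of partial date: "Assume dose date if otherwise".

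A year-only start in another year goes to 1 January of that year. For a month-and-year start in another month, the rule is "If the year and the month is not same as the year and the month of dosing: assume the first of the month for start". For stop dates: "Partial AE stop dates where only the month and year are known: assume the end of the month for stop date".

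Section 7.5 fixes the day count: "Reference start date is defined as the day of the first dose of study drug intervention ie, Day 0". Section 10.1.4 summarises unsolicited events from the day of each vaccination through the following 27 days. Section 10.1.5 summarises serious events from the first vaccination to 364 days after the last, and adds: "A listing of all SAEs including those prior to the first vaccination will be provided at the time of the primary analysis".

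**The concern.** The second branch applies whenever the timing relative to dosing is available. Available timing can be before the dose or after it, and the text gives both the same imputed date. An event that the record shows to have begun before vaccination is therefore moved to Day 0. Separately, no rule stops an imputed start from falling later than the event's own recorded stop date.

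At stake is the classification of individual records. Day 0 and Day 1 both lie in the unsolicited-event window of section 10.1.4, so an event that cannot have been caused by that dose would be tabulated as occurring on the day of vaccination or the day after. The data would also hold records whose start follows their end, a visible integrity fault in a marketing application.

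**Working it through.** There is no sample size, power or alpha figure to reproduce. The check applies the rule as written to test records and compares the result with the reporting window.

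**Inputs from the SAP**
- Imputation branches: section 7.4.
- Study Day = date of event minus date of first dose, with the first dose on Day 0: section 7.5.
- Unsolicited-event window, Day 0 to Day 27: section 10.1.4.

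**Inputs assumed for illustration**
- One dose, on 15 June 2020. Table 1 shows COV002 starting on 29 May 2020 and COV003 and COV005 in June 2020, so the date is plausible.
- A complete stop date of 10 June 2020, where a stop date is used.

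**Results**

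| Recorded start | Timing relative to dose | Imputed start | Study Day | In Day 0–27? | Stop (10 June) minus imputed start |
|---|---|---|---|---|---|
| 2020 | known to be before | 15 June 2020 | 0 | yes | 10 − 15 = −5 days |
| 2020 | not available | 15 + 1 = 16 June 2020 | 1 | yes | 10 − 16 = −6 days |
| June 2020 | known to be before | 15 June 2020 | 0 | yes | −5 days |
| June 2020 | not available | 16 June 2020 | 1 | yes | −6 days |
| May 2020 | known to be before | 1 May 2020 | −(30 + 15) = −45 | no | not in conflict |
| 2019 | known to be before | 1 January 2019 | −(365 + 166) = −531 | no | not in conflict |

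**Reading the table**
1. In rows 1 and 3 the pre-dose timing is on record, yet the event becomes Day 0. This needs no stop date; it follows from the second branch alone.
2. In rows 2 and 4 the timing field is empty, but the stop date shows that the event ended before the dose. If the empty field decides the branch, the start is 16 June. If the stop date is taken as making the timing available, the second branch applies and the start is 15 June. Either way the start follows the end and lies in the window.
3. Rows 5 and 6 bound the problem. A month-and-year start in an earlier month, or a year-only start in an earlier year, stays before vaccination. Complete dates are not touched.
4. A month-only stop date in the dosing month is set to the end of that month and so cannot precede the dose. A stop-date conflict therefore needs a complete stop date before the dose, or a partial one in an earlier month or year.

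**With the change proposed under the fix**, rows 1 to 4 would move to a negative Study Day and leave the window. Rows 5 and 6 would not change.

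**The case against.** The strongest reply is that the approach is openly conservative. Events with a completely missing onset are also included, and placing an event of unknown timing just after the dose is common practice. That stands: the line that adds one day is not at fault for timing that is truly unknown, and the fix keeps it.

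A second reply is that the second branch was meant for events known to relate to a given dose, so that they are assigned to that dose's date. This may be the intent, but the text does not say so.

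A third reply is that the stop date itself makes the timing available, so the day-after branch would not apply. That is a fair reading. It changes the imputed start in the example from 16 to 15 June and does not remove the conflict.

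A reader might also infer more than the document supports:

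- *That pre-vaccination adverse events of all kinds are in the data and are counted as post-vaccination.* Section 10.1.1 describes recording of general events within 28 days after each vaccination. Only for serious events does the SAP say that pre-vaccination records will be listed. Nothing similar is said for other events or for events of special interest.
- *That a sizeable share of month-only onsets must precede the dose.* This would assume that onsets are spread evenly over the dosing month and captured equally before and after the dose. The collection rule in section 10.1.1 does not support that, and no share can be derived.
- *That the summaries of serious events and events of special interest are necessarily affected.* The rules in 7.4 are introduced for summaries by timing relative to each vaccination. Those two summaries instead run from the first vaccination to 364 days after the last, and the SAP does not say whether the imputed dates also select events for them.
- *That events between doses are misassigned to the second dose.* Section 7.4 does not say whether dosing includes dose 2 in the month-and-year rule.

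**Conclusion.** The point holds as a minor defect in a stated rule. Read literally, section 7.4 sets an event known to start before the dose to Day 0, and it allows an event that ended before the dose to be given a start five or six days after its end in the worked example. In both cases the event falls in the unsolicited-event window.

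The conclusion rests on the literal wording and on records of this kind existing. Pre-vaccination serious events are expected, because section 10.1.5 provides for listing them; the presence of other pre-vaccination events is not shown. The SAP does not give the number of partial dates, so the total effect cannot be computed; it is probably small. The rule is identical in both arms, so the likely result is some added background events and some start-after-stop records, with no clear advantage to either arm. The defect does not touch efficacy.

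**What to change.** Amend section 7.4 in three respects:

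1. Limit the rule that assigns the dose date to events known to start on or after that dose.
2. Treat an event as pre-dose if it is known to start before the dose, or if its recorded stop date is before the dose. Its imputed start must be no later than its stop date.
3. Keep dose date plus one day for events whose timing is truly unknown, that is, where neither the before/after information nor the stop date settles it.

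The cost is a few lines of SAP text and the matching change in the program that derives event dates. No new data are needed, and the conservative handling of unknown timing is unchanged.

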## 7.5 Reference Start Date and Study Day

Study Day will be calculated from the reference start date and will be used to show start/stop day of assessments and events. Reference start date is defined as the day of the first dose of study drug intervention ie, Day 0.

Study Day will be computed as follows:

- Study Day = (Date of event – Date of first dose of study drug)

In addition, day relative to vaccination will be derived for each vaccination dose. For example, day relative to the first dose will be equal to the Study Day. Day relative to the second dose will start with a value of 0 on the day of the second dose.

## 7.6 Windowing Conventions

A windowing convention will be used to determine the analysis value for a given study visit for immunogenicity data analyses. The window definitions as following will be used for the immunogenicity.

- A window of  $\pm 14$  days from the target day is applied to the following visits: Study Days 28, 56, 90 and 182;
- A window of  $\pm 30$  days from the target day is applied to the following visits: Study Days 364;

- A window of  $\pm 42$  days from the target day is applied to the following visits: Overall post first dose + 28;

One or more results for a particular immunogenicity variable may be obtained in the same visit window. In such an event, the result with the date closest to the expected visit date will be used in the analysis. In the event that two observations are equidistant from the expected visit date, the later observation will be used in the analysis.

**Table 5 Visit Window for Immunogenicity**

| Dosing Period                 | Visit                        | Day Relative to Dose within the Dosing Period a | Visit Window (Study Day) Relative to the Dosing Period |
|-------------------------------|------------------------------|------------------------------------------------------------|--------------------------------------------------------|
| Period 1 (Relative to Dose 1) | Baseline b        | $\leq 0$                                                   | $\leq 0$                                               |
|                               | Day 28                       | 28                                                         | 14-42                                                  |
|                               | Day 56                       | 56                                                         | 42-70                                                  |
|                               | Day 90                       | 90                                                         | 76-104                                                 |
|                               | Day 182                      | 182                                                        | 168-196                                                |
|                               | Day 364                      | 364                                                        | 334-394                                                |
|                               | Overall post first dose + 28 | 56                                                         | 14-104                                                 |
| Period 2 (Relative to Dose 2) | Day 28                       | 28                                                         | 14-42                                                  |
|                               | Day 56                       | 56                                                         | 42-70                                                  |
|                               | Day 90                       | 90                                                         | 76-104                                                 |
|                               | Day 182                      | 182                                                        | 168-196                                                |
|                               | Day 364                      | 364                                                        | 334-394                                                |
|                               |                              | Scheduled Illness Visit                             | Visit Window (Illness Day)                      |
| Illness Visit                 | Baseline a        | 0                                                          | 0                                                      |
|                               | Illness Day 7                | 7                                                          | 5-9                                                    |

b For each dosing period, the administration of the study intervention is designated as Study Day 0. For analyses within a period, the study day value is incremented by 1 for each date following the vaccine administration. Dates prior to the vaccine administration are decremented by 1, with the date preceding the vaccine administration designated as Study Day 0.

c Where time is available, the time of the collection must be prior to the first dose of study intervention. Day 0 observations taken after the first dose are considered post-baseline values.

d For each dosing period, the administration of the study intervention is designated as Study Day 0. For analyses within a period, the study day value is incremented by 1 for each date following the vaccine administration. Dates prior to the vaccine administration are decremented by 1, with the date preceding the vaccine administration designated as Study Day 0.

## **8. SUBJECT ENROLLMENT AND DISPOSITION**

### **8.1 Subject Identification**

Each subject in the pooled analysis will be uniquely identified by the combination of study number, study site number, and subject number.

### **8.2 Subject Disposition**

Disposition will be summarized by treatment group, for overall and each subgroup.

This disposition table of participants will include the number of participants with informed consent, screen failure, in each exclusion criteria from pooled analysis. For each analysis set defined in Section 5, the number and percentage of participants ongoing in study, completed study, discontinued early from study and reasons of discontinuation, and reasons of exclusion in the analysis set will be provided. Only one reason for study discontinuation will be recorded for each discontinued subject.

### **8.3 Demographics and Baseline Characteristics**

Pooled demography and baseline characteristics data will be summarized for Any dose for Safety analysis set, SDSD + LDSD Seronegative for Efficacy analysis set, SDSD Seronegative for Efficacy analysis set, SDSD + LDSD for Immunogenicity analysis set, and SDSD for Immunogenicity by actual treatment.

Demographics:

- Age (years) at randomization
- Age group (18-64 vs  $\geq 65$  years; 18-55, 56-69 vs  $\geq 70$  years)
- Gender
- Race (Asian, Black, White, Mixed, Other, Unknown)

Baseline characteristics:

- BMI at baseline ( $< 30$  vs  $\geq 30$  kg/m^2)
- Serostatus at baseline (Negative, Indeterminate, Positive)
- Cardiovascular Disorder (Yes vs No)
  - Subcategories: chronic heart failure, ischaemic heart disease (including angina), atrial fibrillation, peripheral vascular disease, valvular heart disease, hypertension, myocardial infarction and other
- Respiratory disease (Yes vs No)
  - Subcategories: Chronic obstructive pulmonary disease, Bronchiectasis, Asthma, Other

- Diabetes (Yes, No, Not collected)
  - Subcategories: Type 1 diabetes, Type 2 diabetes not using insulin, Type 2 diabetes using insulin, Other
- Current smoker (Yes vs No)
- Former smoker (Yes, No, Not collected)
- Comorbidity at baseline (at least one comorbidity vs no comorbidity), where comorbidity includes BMI  $\geq 30$  kg/m^2 at baseline, Cardiovascular Disorder, Respiratory disease or Diabetes.

Missing due to participant not providing the answer will be presented under category “Missing” while missing due to information not collected in specific study will be presented under category “Not collected”.

